### Ethical and Research Governance Approval

This trial was approved by the Ethics Committee of the Institute of Research in Primary Care of Catalonia Institut Universitari d’Investigació en Atenció Primària Jordi Gol and given funding through the competitive call: Health Research and Innovation Strategic Plan 2016-2020 of the Catalan Government (ID:SLT002/16/00197).

### Participants

This trial is being conducted in 7 public-based primary health care centers for sexual and reproductive health of Catalonia in the cities of Mataró, Badalona, Santa. Coloma de Gramanet, Granollers, Mollet, Cerdanyola-Ripollet, and Sabadell. Participants to the study are being recruited in each of the primary health care centers according to the following *inclusion criteria*: Young people 16 to 24 years old, diagnosed with at least 1 of the curable STIs (syphilis, gonococcus, or chlamydia). Partners who have had sexual contact within the previous 6 months since the diagnosis of index case.

*Exclusion criteria* are the following: diagnosis of other STIs (trichomonas, HIV, Hepatitis C, and Hepatitis B), which, although partner notification is advisable, will not be included to prevent complexity in the study. Under the diagnosis of 1 of these STIs, health professionals will perform according to the current clinical guidelines.

### Study Period

The study will be conducted within a 3-year period. A total of 1 year to prepare the Web app, 18 months for the field work, and 6 months for the evaluation and dissemination of results.

### Groups of the Study

#### Control Group

Those receiving the recommendation to inform their partners about exposure to STIs by the standard procedure currently available in the Catalan guidelines, use of a Partner notification paper card.

#### Game Intervention Group

Those advised to enter the *Notijoves* Web app with a code and follow the steps of the game to finally choose among different ways to notify their partners.

#### Web App Direct Intervention Group

Those advised to enter the *Notijoves* Web app with a code and directly choose among different ways to notify their partners.

### Main Outcome Variable

The main outcome variable of the study is the percentage of partners informed of their exposure to a STI from their index cases, according to the assigned study group.

### Sample Size

Young population accessing all centers of study within a year is around 400. They have been randomly distributed in 3 arms, according to the Bonferroni correction, to allow multiple comparisons of outcomes with a significance level of *P*=.016. The trial is expected to have 10% of withdrawals after recruitment within the intervention groups and 20% of withdrawals after recruitment within the control group. Therefore, to have at least 120 participants in each 1 of the groups, 133 are recruited in each 1 of the intervention groups and 150 are recruited in the control group. The random list ratio is 1:1:1.28. To achieve this sample, participant recruitment is allowed for a period ranging from 13 to 18 months.

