**Methods:**

This is a multicenter randomized controlled trial with a proportional stratification of the sample by center and random allocation of participants to the 3 arms of the study (simple Web-based intervention, game Web-based intervention, and control). This study is being conducted by midwives, gynecologists, and physicians in the sexual and reproductive areas of the primary health care centers.

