## Methods

### Design

This is an unblinded 3-armed randomized controlled trial, assigning patients to each arm of the study through the proportionally stratified sample of patients by health center, which will test the primary hypothesis that a greater proportion of partners will be informed about their exposure to STIs (syphilis, chlamydia, or gonococcus) in the intervention groups compared with the control group. We will randomize 416 young and recently diagnosed index cases in 1 of the 7 centers of the study. The researcher responsible for analyzing the data will be blind to group allocation.

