### Data Analysis

Descriptive analysis of index cases visiting health centers will be baselined to further assess differences in yield by groups. Chi-square test and Student *t* test for categorical and continuous variables will be used to assess differences in baseline characteristics among groups. Regression analysis and adjusting for confounding variables will be used to evaluate the primary outcome and relative risk, and its 95% CIs will be calculated. Significance will be set at .05. The multiple imputation method will be used to generate possible values for missing values. This is considered the gold standard for dealing with missing values. Data will be analyzed in Stata v12 (StataCorp LLC).

The methodology of analysis of the social and sexual networks will be used from an egocentric perspective. Structural measures of the network will be calculated, such as the size of the network, number of direct links, density, the geodesic average distance, diameter of ego’s network, and measures of centrality, such as the degree of intermediation of a contact or index case. Furthermore, we will compare social network, density, and structure. Network measurements will be done using the R statistical package.

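### If the Bonferroni level of .016 is carried into the analysis, it is needlessly conservative for three arms: a closed test or Holm keeps family-wise error at .05 with more power

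*Protocol article*

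**What the plan says.** The Design section describes the trial with "This is an unblinded 3-armed randomized controlled trial" and frames the primary hypothesis as a higher proportion of informed partners "in the intervention groups compared with the control group". The Main Outcome Variable section defines the outcome as "the percentage of partners informed of their exposure to a STI from their index cases".

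Multiplicity appears once, in the Sample Size section, where participants are distributed over the arms "according to the Bonferroni correction, to allow multiple comparisons of outcomes with a significance level" of .016. The same section sets the target "to have at least 120 participants in each 1 of the groups". It states no effect size, notification rate or power.

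The Data Analysis section says "Significance will be set at .05" and plans relative risks with 95% confidence intervals. It mentions neither .016 nor Bonferroni, and it gives no order of tests.

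**The concern.** The level .016 corresponds to division by three, so the family appears to be game versus control, direct web versus control, and game versus direct web. Single-step Bonferroni makes no use of the logical link between these hypotheses: if any two of them are true, the third is true as well. With three arms that link lets the pairwise tests run at .05 behind a three-arm test at .05, without giving up family-wise control.

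Power is at stake in a trial where it is scarce. The Results section reports about 6 recruitments per month and recruitment slower than expected. A stricter threshold than the error control requires makes a useful web tool harder to demonstrate, and relaxing it needs no extra participants.

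**Working it through.** **Inputs from the article.** Three arms; per-comparison level .016; 120 evaluable per arm; withdrawals of 10% (intervention) and 20% (control). Effect size, power and sidedness are not given. I assume two-sided tests and show a range.

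**The plan's own figures.** 120/0.9 = 133.3 (stated 133); 120/0.8 = 150; 133 + 133 + 150 = 416. The level is .05/3 = .01667, truncated to .016. The 120 itself cannot be derived from the article. As a plausibility check, a 20-point difference at .016 with 80% power needs 110 to 131 per arm for control rates of 20% to 60%.

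**Error control of the closed test.** Write C, G and W for control, game and direct web. The pairwise nulls are G=C, W=C and G=W. Any two together give G=W=C, so the closed family has four members: the global null and the three pairs. A pair is rejected only if both the global test and its own test have P ≤ .05.
- All arms equal: any false rejection requires the global test to reject, which has probability .05.
- Exactly one pair equal: there is one true null, tested at .05.
- No pair equal: no false rejection is possible.

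Simulation agrees. With normal approximations (400,000 trials), the closed test's family-wise error is .050 under the global null and .050 for the one true null when the third arm is far away. Bonferroni at .016 uses .042 and .016. With binary data at 120 per arm, the global-null rates are 4.4% (Bonferroni) and about 5.2% (closed), within the large-sample approximation.

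**Power, equal effects of both web arms** (normal approximation, 120 per arm; rows are labelled by assumed power at .05/3):

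| Assumed power | Bonferroni .016 | Closed | Gain (points) |
|---|---|---|---|
| 50% | 49.4% | 60.2% | 10.8 |
| 60% | 59.4% | 70.2% | 10.8 |
| 70% | 69.5% | 79.4% | 9.9 |
| 80% | 79.6% | 87.8% | 8.2 |
| 90% | 89.8% | 94.9% | 5.1 |

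**Power, direct web with half the effect of game.** The largest contrast (game versus control) gains 5.1 points at 50% assumed power (49.3% to 54.4%), falling to 1.8 at 90% (89.8% to 91.6%). The two smaller contrasts gain 9.1 points at 50% (11.2% to 20.3%), rising to 16.4 at 90% (28.5% to 44.9%).

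**Power, binary outcome** (300,000 trials, 120 per arm, one independent result per index case):
- Control 50%, both web arms 70%: 78% (Bonferroni .016), 81% (Holm) and 87% (closed) per web-versus-control comparison. Power to show both is 66%, 72% and 82%.
- Control 40%, game 60%, direct web 50%: game versus control goes from 77% to 80%, and game versus direct web from 20% to 33% (Bonferroni to closed).

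**Holm.** The ordered P values are compared with .05/3, .05/2 and .05. Each threshold is at least .016, so Holm rejects whatever Bonferroni at .016 rejects.

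**Where the closed test rejects less.** With the third arm midway, the 2-df statistic is close to the squared z of the extreme pair. The gate needs 5.99 (z = 2.45), while .016 needs z = 2.41. Example: 34, 43 and 52 informed out of 120 give P = .0154 for the extreme pair but a global P = .053. Bonferroni rejects and the closed test does not. Such data sets made up at most about 0.15% of simulated trials.

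**The case against.** Single-step Bonferroni is a standard, valid procedure, and preferring another valid procedure could be called taste; the detailed testing rule may also sit in an analysis plan that is not shown. It is true that nothing here is invalid. But the article itself names a rule and a level, and the point concerns that stated choice.

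Three stronger readings are tempting, and the article supports none of them.
- A reader might infer that testing each pair at .016 is fixed for the analysis. The figure stands only in the Sample Size section. Sizing at .016 is compatible with a later closed or Holm analysis, and the Data Analysis section says .05. That .05 could be the family-wise level or an uncorrected one. If it is uncorrected, the power is kept only by giving up the control that the Bonferroni correction was meant to provide.
- A reader might infer a loss of about 8 points per comparison. That figure needs 80% power and equal web effects, neither of which is stated. With equal web effects, game versus direct web is a true null and has no power to lose.
- A reader might infer that the closed test always finds more than Bonferroni. The 34/43/52 example shows otherwise; only Holm is never worse.

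Two further objections stand as limits. The outcome counts partners, who cluster within index cases, so the absolute power figures are illustrative; the closure argument is unaffected. Bonferroni also has matching simultaneous confidence intervals, a legitimate reason to choose it.

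**Conclusion.** The point holds in conditional form: should single-step .016 be the analysis rule, it gives up power with no need for it in family-wise control. The size depends on unstated effects, so the 5 to 11 points (equal web effects, 50% to 90% power) and the 2 to 16 points (one effect half the other) are ranges under assumption, not figures of this protocol. They rest on 120 independent index cases per arm, two-sided tests and large-sample approximations. The change ranks between optional and recommended. What has to be settled in any case is which of the two stated levels applies to the pairwise tests.

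**What to change.** State one rule, in the same words, in the Sample Size and Data Analysis sections. Either of these will do:

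1. Closed test: a 2-df test of equality of the three arms from the primary model at .05; only if it is significant, each pairwise relative risk at .05. Report as adjusted P the larger of the global and the pairwise P value.
2. Holm over the three pairwise tests, if the sponsor prefers no global gate or wants a rule that never rejects less than Bonferroni. Its gain is smaller (78% to 81% against 78% to 87% in the 50/70/70 example).

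Say also that .05 is the family-wise level. The choice should be made before outcome data by arm are examined.

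The cost is wording only, with no extra participants. The downside of the closed test is in the intervals: the planned pairwise 95% confidence intervals are not simultaneous, and one may exclude a relative risk of 1 when the gated test is not significant. They should be labelled as unadjusted and shown beside the adjusted P value.

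### The stated random list ratio of 1:1:1.28 contradicts the arm sizes 133:133:150, the total of 416 and Table 1, which all imply 1:1:1.128; probably a misprint, but the programmed list should be checked

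*Protocol article*

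**What the plan says.** The Sample Size section works back from a target after withdrawals: "to have at least 120 participants in each 1 of the groups". It assumes "10% of withdrawals after recruitment within the intervention groups" and "20% of withdrawals after recruitment within the control group". From these it derives the recruitment targets: "133 are recruited in each 1 of the intervention groups and 150 are recruited in the control group". The next sentence reads: "The random list ratio is 1:1:1.28".

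The Design section gives the total: "We will randomize 416 young and recently diagnosed index cases". Table 1 breaks this down by centre and arm, with column totals of 150 control, 133 game and 133 direct web. According to the sections on randomization and data collection, the arm is assigned by a random code that the health professional draws from the web app.

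**The concern.** An allocation ratio and a set of arm sizes carry the same information, so they must agree. Here the ratio is printed directly after the arm sizes and gives a clearly larger control share. It is labelled as the ratio of the random list, which is the figure a programmer would be expected to use.

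There are two possibilities. Either the printed ratio is wrong and the list follows Table 1, in which case only the publication needs correcting. Or the list was built at 1.28, in which case the trial would not produce the planned arm sizes, and the two intervention arms would fall below the protocol's own minimum at the planned total.

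**Working it through.** **Inputs.** From Sample Size: 120 per arm after withdrawals; withdrawals of 10% (each intervention arm) and 20% (control); targets 133, 133 and 150; list ratio 1:1:1.28. From Design: total 416. From Table 1: the arm counts by centre. The ratio is read with control as the larger arm, the only reading that fits the targets.

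**1. The arm sizes reproduce.** Formula: n/(1 − d).
- Intervention: 120/0.90 = 133.3, stated as 133.
- Control: 120/0.80 = 150, as stated.
- Sum: 133 + 133 + 150 = 416, as stated in Design.

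**2. The ratio does not.**
- From the stated targets: 150/133 = 1.128.
- Before rounding: 150/133.3 = 1.125.
- With the cruder inflation n(1 + d): 132 and 144, ratio 144/132 = 1.09.

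None of these gives 1.28.

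**3. Table 1 does not support 1.28 either.** Control divided by one intervention arm, by centre:

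| Centre | Control / intervention | Ratio |
|---|---|---|
| Badalona | 30/26 | 1.15 |
| Sabadell | 27/24 | 1.13 |
| Granollers | 27/24 | 1.13 |
| Mollet | 20/18 | 1.11 |
| Mataró | 20/17 | 1.18 |
| Santa Coloma | 14/13 | 1.08 |
| Cerdanyola | 12/11 | 1.09 |
| All | 150/133 | 1.128 |

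The rows run from 1.08 to 1.18, so rounding within centres does not explain 1.28. Conversely, with 133 in each intervention arm, 1.28 would require 133 × 1.28 = 170 controls and a total of about 436.

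**4. What a list at 1.28 would give with 416 patients.** The shares add to 1 + 1 + 1.28 = 3.28.

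| | Each intervention arm | Control |
|---|---|---|
| Randomised at 1:1:1.28 | 416/3.28 = 126.8 | 1.28 × 126.8 = 162.3 |
| After withdrawals | 126.8 × 0.90 = 114.1 | 162.3 × 0.80 = 129.9 |
| Randomised at 1:1:1.128 | 133 | 150 |
| After withdrawals | 133 × 0.90 = 119.7 | 150 × 0.80 = 120.0 |

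At 1.28 each intervention arm ends about 6 short of 120 (5%) and control about 10 above it. Reaching 120 per intervention arm at that ratio would need (120/0.90) × 3.28 = about 437 patients, some 21 more than planned. At 1.128 the plan meets its target apart from rounding.

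**5. Effect on power.** The article gives no effect size, so the proportions below are assumptions. The calculation is a simple two-proportion comparison at two-sided alpha 0.05/3 (the article states .016), treating each index case as one binary observation.

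| Assumed proportions | As planned, 120 vs 120 | Intervention vs control at 1.28, 114 vs 130 | Intervention vs intervention at 1.28, 114 vs 114 |
|---|---|---|---|
| 50% vs 70% | 78.4% | 78.8% | 75.9% |
| 40% vs 60% | 76.4% | 77.0% | 73.9% |
| 40% vs 55% | 47.3% | 47.9% | 44.9% |

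The larger control arm offsets the smaller intervention arms. Only the comparison between the two intervention arms loses, by 2 to 3 percentage points.

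**The case against.** The best defence is that this is a one-digit misprint: 1.28 is 1.128 with a digit missing. The derivation, the total and Table 1 all point to 1.128, so a careful reader can recover the intended allocation. A list built from the counts in Table 1 would give 133:133:150 whatever ratio is printed. This stands as the most likely explanation. It does not make the printed figure right, and it does not show what was programmed.

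A reader might infer that the trial is in fact randomising at 1.28 and that the intervention arms will fall short. The article does not support that. The first 32 allocations (15 control, 9 game, 8 direct web) cannot settle it: treating allocations as independent, 15 or more controls has probability about 0.14 at 150/416 and about 0.23 at 1.28/3.28. A reader might also take the shortfall as a loss of power for the primary hypothesis. That hypothesis compares intervention with control, and power there is essentially unchanged.

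It is also tempting to compute a worse case in which recruitment stops at 150 controls. The article has no such rule; it fixes only the total of 416.

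Finally, the article reports about 6 recruitments per month, so total accrual will affect arm size far more than six patients per arm. That is fair and limits the importance of the point, but a contradictory allocation figure still needs correcting.

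**Conclusion.** The contradiction is certain: 1:1:1.28 cannot be reconciled with 133:133:150, with 416, or with Table 1, and 1:1:1.128 fits all three. That it is a misprint is probable but not proven.

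The consequence is conditional and modest. It arises only if the list was built at 1.28 and recruitment ends at 416. The expected split is then about 127:127:162, or 114:114:130 after withdrawals. The intervention arms would miss the stated 120 by about 5%, with little change in power against control and a small loss between the two intervention arms. The arm sizes rest on the article's planning values for withdrawal, and the power statement on assumed proportions. This is a needed correction of a stated figure, not evidence that the trial is underpowered or wrongly randomised.

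**What to change.** 1. Correct the list ratio in Sample Size to 1:1:1.128, and print the counts 133:133:150 beside it.
2. Check the list programmed in the web app against Table 1. Someone other than the analyst should do this, since the article says the analyst is blind to allocation.
3. If the list follows Table 1, nothing more is needed. If it was built at 1.28, report that ratio as the one used and restate the expected arm sizes: about 127:127:162 randomised and 114:114:130 after withdrawals.

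The cost is one figure in the text and one check of an existing list, plus a short restatement if 1.28 was used. Rebuilding the list during recruitment is not advised. It would change the allocation probabilities over calendar time, need an amendment and complicate the analysis, for almost no gain in power against control.

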### Randomization and Informed Consent Procedure

The sample is proportionally being assigned to each of the 7 centers, according to their regular activity (see Table 1).

The health professional proposes that the young patient index case should participate in the study, and once verbal acceptance is obtained, he gets into the Web app (see Figure 1) to obtain a random code that assigns the patient to 1 of the 3 arms of the study. He also prints the informed consent to be signed by the patient and explains all the procedures to him/her, according to the arm assigned (control, direct Web app, and game Web app). A copy of the Informed consent is given to the patient, and the original is kept under the custody of the health professional in the participating center.

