### Participation Procedure

All the candidates who accept to participate in the study are given information about the study, both verbally and by receiving an Information sheet. The candidates refusing participation are also asked to complete a quick survey (2 questions) to provide reasons for not participating. (see Figure 2)

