### Control Group

The control group receives usual partner notification advice, and the health professional prints as many partner notification paper cards as the patient index case mentions to be able to provide partner notification paper cards to exposed partners. Therefore, exposed partners are expected to receive a partner notification paper card and a letter that are to be given to their health professional. The letter informs of the potential diagnosis and advised treatment. The card has information of the STI and the list of Sexual and Reproductive Health Centers and primary health care centers for sexual and reproductive health, where the recipient of the notification can go for diagnosis and potential treatment.

The random code given to the index case patient appears in the informed consent and in a short paper questionnaire (12 questions). Each 1 of the partner notification paper cards has a code in line with the study arm of the index case. This means that partners receiving a partner notification paper card from an index case assigned to the control arm are kept in the control arm themselves.

**Table 1 table1:** Sample size distribution for each primary health care center for sexual and reproductive health.

Location of health care centres^a^	Control^b^ N1	Intervention game^c^ N2	Intervention Web^d^ N3	Total N
Badalona	30	26	26	82
Sabadell	27	24	24	76
Granollers	27	24	24	74
Mollet	20	18	18	57
Mataró	20	17	17	55
Santa Coloma	14	13	13	40
Cerdanyola	12	11	11	34
Total	150	133	133	416

^a^Primary Health Care Centres for Sexual and Reproductive Health.

^b^Control group.

^c^Game intervention group.

^d^Web app direct intervention group.

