### Web App Game Intervention Group

Individuals assigned to this group receive an Information sheet explaining the objectives and procedures of the study. After providing a signature of their informed consent, they receive a paper copy of this informed consent that has a specific code through which they enter the game by connecting to the *Notijoves* Web address. A paper card with the “Notijoves” Web address is given to the patients. Once they enter the Web app, they are asked to feed the given code into the field of Young PANDORA screen.

By entering the code, they start playing the game, and they are directed through different screens and situations. A Web-based questionnaire is inserted in the game. At the end of the game, they are also asked to respond to a satisfaction questionnaire.

The game is expected to motivate the youngster to notify partners of their exposure to an STI. While playing the game, the youngsters are asked to answer questions related to the clinical symptoms, prevention, and control of their recently diagnosed STI. Like this, they *learn by playing.* Another feature of the Web app is the link to advisory videos on how to approach the *face-to-face* notification of exposure to an STI. Finally, the game ends with a screen, where the youngsters can choose from among the different electronic tools to notify (short message service, email, or WhatsApp) either anonymously or by identifying themselves.

The electronic partner notification card has the following: (1) a code automatically assigned by the electronic system that is concordant with the arm where the index case patient entered the study, (2) the informative message advising the partner to visit a health center for diagnosis and potential treatment, and (3) a link to a list of health centers of the study and the Web app address, where the partner could go and where the informed partner could enter and participate in the study by introducing the code. Along with the notification card, the partner receives an electronic letter to be given to the health professional for him to be aware of the STI diagnosed to the sender of this notification and the advised treatment.

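### The arm is drawn and explained after verbal acceptance but before written consent, so refusal to sign can depend on the allocation

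*Protocol article*

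**What the plan says.** The section Randomization and Informed Consent Procedure sets out the steps. The professional proposes the study. Then "once verbal acceptance is obtained, he gets into the Web app (see Figure 1) to obtain a random code", and that code fixes the arm. The next sentence reads "He also prints the informed consent to be signed by the patient and explains all the procedures to him/her, according to the arm assigned". The signature is thus still to come when the arm is known and described.

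The arm-specific sections agree:

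- Control Group: "The random code given to the index case patient appears in the informed consent", so the code exists when the form is produced.
- Web App Game Intervention Group: the section starts from people already assigned, who are given the information sheet and sign. It continues "After providing a signature of their informed consent, they receive a paper copy of this informed consent that has a specific code".
- Web App Direct Notification Intervention Group: the same sequence as for the game arm.

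On refusal, the section Participation Procedure says "The candidates refusing participation are also asked to complete a quick survey (2 questions) to provide reasons for not participating". The questionnaire list under Data Collection gives what is recorded for people who do not participate: their reasons, and whether they are an index case or a recipient. Arm is not listed. The Design section describes the trial as unblinded.

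**The concern.** Randomisation makes the arms comparable at the moment of allocation. If patients can still decline once they know the arm, those who remain are comparable only if declining is unrelated to the arm or to notification behaviour. The offers differ visibly (a paper card, a web app, or a game leading to the same app), so equal willingness to sign cannot be taken for granted.

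At stake is the primary comparison, the percentage of partners informed by arm. A patient who is allocated but does not sign answers no index-case questionnaire as a participant. Nothing in the article says that such patients are counted by arm or kept in the analysis. The planned covariate adjustment and multiple imputation work on patients who are in the dataset, and the blinded analyst does not see who failed to enter it. The Limitations section names several biases but not this one.

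**Working it through.** **1. Order of steps.** Taken together, the sections give:

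| Step | Where stated | Arm known? |
|---|---|---|
| Study proposed | Randomization and Informed Consent Procedure | no |
| Verbal acceptance | same | no |
| Code drawn, arm fixed | same | yes, to the professional |
| Form printed, assigned procedure explained | same; code on the form per Control Group and both web-app sections | yes, to both |
| Signature | same; both web-app sections | yes |

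No section places the signature before the code. The exposed interval runs from verbal acceptance to signature.

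**2. The plan's own attrition figures.** The Sample Size section assumes 10% loss in each intervention arm and 20% in control. These reproduce the recruited numbers: 120/0.90 = 133.3 (133 stated), 120/0.80 = 150, and 133 + 133 + 150 = 416. The control figure is worded as "20% of withdrawals after recruitment within the control group". It is a later loss, not refusal to sign, so the document holds no figure for this step.

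**3. Size under stated assumptions.** Let r be the fraction of an arm that declines after learning the arm, s the percentage of partners informed by signers, and d the percentage that decliners would have informed.

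- Rate in the arm as randomised: (1 − r)s + rd
- Rate observed among signers: s
- Bias: s − [(1 − r)s + rd] = r(s − d)

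Assume s = 55%, d = 30%, and refusal in control only:

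| r | Bias in the control rate |
|---|---|
| 5% | 0.05 × 25 = +1.25 points |
| 10% | 0.10 × 25 = +2.5 points |
| 20% | 0.20 × 25 = +5 points |

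This raises the control rate and so understates any benefit of the app. If decliners were instead the keen notifiers, say d = 80%, the same r gives −1.25 to −5 points and overstates it.

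**4. Sensitivity to the assumptions.** Suppose the full arm would have informed 50% and refusal occurs in one arm only. The observed rate is (50 − rd)/(1 − r), with d in percent.

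| r | d = 25% | d = 0% |
|---|---|---|
| 5% | +1.3 | +2.6 |
| 10% | +2.8 | +5.6 |
| 20% | +6.3 | +12.5 |

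If all arms lose the same fraction of the same kind of patient, and there is no true arm effect, the difference between arms is unbiased.

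**5. Early counts.** The Results section reports 15 control, 9 game and 8 direct web. Under 150:133:133, the expected counts for 32 patients are 11.5, 10.2 and 10.2 (chi-square 1.67 on 2 df, p = 0.43). Under the stated 1:1:1.28 they are 12.5, 9.8 and 9.8 (chi-square 0.88, p = 0.64). There is no sign of a shortage of controls, but 32 patients are too few to exclude selection.

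**The case against.** The strongest reply is that the patient agrees before any code exists. The professional also proposes the study without knowing the arm, and nothing suggests that the code can be foreseen. That stands. A reader might infer that allocation concealment has failed in the usual sense, with professionals choosing whom to approach according to the next arm. The text does not support this. What is exposed is a change of mind between verbal and written consent, which is a shorter interval than the whole decision to join.

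A reader might also take the doubled withdrawal expected in control as evidence that controls will refuse to sign. As shown above, those figures describe loss after recruitment and cannot be used for this step.

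Two further points limit the concern. Under Data Collection, the professional's web entry both draws the code and registers the diagnosis. Codes issued are therefore probably recorded by arm, and non-signers could be counted and the bias bounded, although their outcomes would still be missing. The participation algorithm (Figure 2) is not reproduced in the text available, and the article condenses a fuller protocol, so safeguards may exist that cannot be seen here. Neither point changes the order that the article itself fixes.

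**Conclusion.** The point holds as a design weakness: the allocation is known to patient and professional before written consent, so selection after randomisation can occur. The stronger statement, that the arms have been selected, is not supported, since the document reports no refusals by arm and the early counts show no imbalance. The size and direction are unknown. The 1.25 to 5 points apply only if 5% to 20% of controls and no others decline, with decliners at 30% and signers at 55%. None of these values is in the document, and the sign can reverse. The case for correction rests on the order of steps and the ease of changing it, not on that illustration.

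**What to change.** Give the information sheet and obtain the signature on a single consent form that describes all three arms. Have the web system require confirmation of signed consent before it releases a code, and only then explain the assigned procedure.

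The code is now printed on the consent form, and in the web arms the patient's copy is how the code reaches the patient, so its delivery must change too. Either add the code to the form after signature, or give it on a separate slip or on the web-address card already handed out.

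For patients already allocated, report codes issued against consents signed by arm, and keep allocated non-signers in the flow diagram. For refusals from now on, record whether they came before or after the code and, if after, the arm.

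The cost is a revised form, an ethics notification and one required field in the professional's web entry. No extra visits or staff are needed. The Results section reports that access problems with the web system had already delayed recruitment, so the new field should be tested before release. With 32 of the planned 416 patients assigned at the early-June 2018 count, a change would protect most of the sample.
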